# Effects of Acute Exercise on Drug Craving, Self-Esteem, Mood, and Affect in Adults with Polysubstance Use Disorder: Protocol for a Multicenter Randomized Controlled Trial

**DOI:** 10.2196/18553

**Published:** 2020-10-13

**Keywords:** exercise, acute, substance abuse, physical activity, drug addiction

## Abstract

**Background:**

Novel treatments for substance use disorders are needed. Acute bouts of exercise can improve mood states and craving in nonclinical populations. Exercise effects in those with polysubstance dependence are understudied; controlled trials are needed.

**Objective:**

This protocol describes a clinical study examining the short-term psychological effects of 2 types of physical activity, soccer and circuit training, in patients with substance use disorders. Effects will be compared with a nonexercise control group. Specific aims are to investigate whether there are differences between the activities and the duration of changes.

**Methods:**

This study is a short-term multicenter randomized control trial with a crossover design. Patients consecutively admitted to 4 inpatient treatment centers were invited to participate in 3 conditions, each lasting 45 minutes, within one week. The order of the conditions was randomized. There were a total of 5 assessments, taken at baseline, immediately before each condition, immediately after each condition, and 1, 2, and 4 hours postintervention, enabling patterns of change over time to be observed. Psychological effects were assessed with self-report questionnaires, which included scales for craving, state anxiety, positive and negative affect, self-esteem, and mood. Exercise intensity was assessed with the Borg Rating of Perceived Exertion scale and a heart rate monitor (Polar M200; Polar Electro Ltd). Cortisol was assessed in saliva before and 4 hours after the intervention.

**Results:**

A total of 39 patients were included in the study. Data collection was completed in 2019.

**Conclusions:**

We anticipate larger improvements in the intervention groups than among controls, indicating positive psychological effects during and after exercise. The study will add clinically relevant information about the short-term psychological effects of exercise in the treatment of substance use disorders, using activities that are easily accessible in different clinical settings.

**Trial Registration:**

German Clinical Trials Register DRKS00018869; https://www.drks.de/drks_web/navigate.do?navigationId=trial.HTML&TRIAL_ID=DRKS00018869

**International Registered Report Identifier (IRRID):**

DERR1-10.2196/18553

## Introduction

Substance use disorders (SUD) have wide-reaching impacts on health and well-being and contribute substantially to the global disease burden [1]. They are associated with shorter life expectancy, and comorbid medical conditions are common [2]. The prevalence of co-occurring personality and other psychiatric disorders is high, with estimates ranging from 50% to 90% [3]. Mood and anxiety disorders are prevalent and affect both the severity and outcome of treatment [4]. Current treatment options for SUDs include cognitive behavioral therapy, motivational interviewing, and medication. Although documented as effective, these methods do not help all patients. Relapse rates range between 40% and 60% [5], and dropout rates from in-patient treatment is around 30% [6].

Despite their high prevalence, few people with SUDs ever receive treatment, and there is a need for more treatment options [7,8]. One potential explanation for poor help seeking is the perceived stigma associated with traditional treatments [9,10]. Lifestyle-focused interventions have potential to increase help seeking by reducing this stigma.

Physical activity has been suggested as an alternative or complementary treatment option for SUDs [11-13]. The rationale is that physical exercise might be effective due to its beneficial effects on factors related to relapse and the maintenance of the disorder, such as comorbid mental disorders, craving, and emotional dysregulation [14-17].

Regular physical activity increases fitness and lowers the probability of chronic diseases [18,19]. It has been proposed as a strategy for alleviating symptoms of psychiatric disorders in general [20,21], and its application in the mental health care system is increasing. Regular physical activity has been shown to be effective in the prevention and treatment of common mental health conditions [22]. Studies also indicate that physical activity alleviates symptoms in people suffering from severe mental disorders [23]. Acute bouts of exercise have cognitive and mood-enhancing benefits, including improved executive functioning and lower state anxiety and stress reactivity [24,25]. The mechanisms behind the psychological benefits of exercise in SUDs are not well established, but one tenable hypothesis is that they are partly mediated by changes in the stress hormone cortisol [24].

While the effects of exercise are well documented for common mental disorders, there has been less research focus on SUDs. Most studies have addressed the effect of chronic exercise interventions on smoking cessation or alcohol misuse. Long-term exercise programs might affect smoking behavior [26] and lower tobacco cravings [27]. A meta-analysis of 21 exercise studies for alcohol use disorder concluded that, while regular exercise did not seem to affect consumption, it had beneficial effects on depression and physical fitness [28]. In another meta-analysis, Wang et al [29] found that exercise was associated with greater abstinence rates among illicit drug users compared with those using alcohol and nicotine. The effect of exercise on withdrawal symptoms, anxiety, and depression was not moderated by the type of substance used. Colledge et al [30] reviewed the effects of anaerobic exercise on SUDs. The results were mixed, with some evidence of a positive effect on abstinence from nicotine. No conclusions could be drawn regarding the effects of exercise among illicit drug users.

One plausible explanation for the beneficial long-term effects of an exercise program is that many single sessions have a cumulative long-term benefit. Few studies have addressed the short-term effects of physical activity in SUDs. A study of 45 regular smokers found that bouts of moderate and vigorous exercise provided relief from withdrawal symptoms, while moderate exercise relieved distress and improved mood [31]. Studies addressing alcohol urges or cravings show promising results, with lower craving after low-to-moderate intensity exercise [13,32]. Wang et al [33] studied the development of craving for amphetamines and found a reduction in cravings during and immediately after stationary cycle exercise. Results suggest that the intensity of the exercise may affect craving, with the lowest craving following moderate-to-vigorous exercise [34].

The misuse of a single substance is exceptional in SUDs [35]. Whether acute exercise can benefit people with polysubstance dependencies is unclear. Most studies have assessed aerobic forms of exercise, often in laboratory conditions using stationary bicycles [12,28]; little is known about other forms of exercise in clinical settings. With some exceptions [25], psychological benefits across different forms of exercise have not been compared, and it is unclear how long the changes last following a single exercise session. Studies have mostly used pre- and postassessments only, which is a limitation.

To address these questions, we conducted a feasibility study to compare the short-term effects of 3 different exercises (soccer, circuit training, and walking) conducted in nonlaboratory settings [36]. Findings suggested that moderately intense exercise activities performed in natural settings may increase mood, help attenuate drug cravings, increase positive affect, decrease negative affect, and improve self-esteem. The results were promising but need to be replicated with a larger sample and a randomized design.

In this study, we are conducting a multicenter randomized controlled trial to compare the short-term effects of 2 forms of exercise (soccer and circuit training) with a control condition (a lecture on the health benefits of physical activity) in polydrug-dependent inpatients. We chose to compare the effects of exercise to a nonexercising control group (lecture) instead of a walking-based intervention, as previous studies have shown that even light physical activity can have mood-enhancing effects [37]. We are also performing biomarker analyses of cortisol to better understand the underlying mechanisms.

Key research questions that will be addressed include (1) What are the short-term effects of soccer and circuit training on mood (primary outcome), drug craving, positive and negative affect, state anxiety, and self-esteem in adults with SUD? (2) How long do the effects last after the exercise sessions end? (3) Are there differences between the two forms of exercise? (4) Do the effects differ with the intensity of the exercise? and (5) Are the study outcomes associated with changes in the stress hormone cortisol?

Based on previous studies [33,38], we hypothesize that there will be positive psychological effects on the study outcomes after exercise, with a reduction in craving and an improvement in mood and affects. We expect to find larger improvements in the intervention groups than in the control group.

## Methods

We adhered to the SPIRIT (Standard Protocol Items: Recommendations for Interventional Trials) guidelines in the preparation of this protocol. The study will be reported according to CONSORT (Consolidated Standards of Reporting Trials) ethical guideline recommendations.

### Ethics Approval and Consent to Participate

The trial is approved by the Regional Committee for Medical and Health Research Ethics in South East Norway (2018/1275) and was retrospectively registered with the German Clinical Trials Register on November 11, 2019 (DRKS00018869). Before inclusion in the study, participants were asked to sign an informed consent form. All patients agreed to participate voluntarily and were told they were free to withdraw from the study at any time.

### Setting and Participants

Inpatients from 4 treatment facilities were invited to participate. The main site for the study was the Department of Addiction Treatment - Adult, Division of Mental Health and Addiction, Oslo University Hospital. In addition, 3 other treatment centers were asked to participate (2 accepted): the Department of Addiction Treatment - Youth, Oslo University Hospital; an inpatient treatment center at the Division of Mental Health and Addiction, Vestfold Hospital Trust; and the Blue Cross Treatment Center, Slemdal, Oslo. The study was conducted in a clinical setting, where the participants received treatment.

The treatment centers are staffed by medical doctors, nurses, psychologists, and social workers. Treatment includes individual and group counseling and pharmacotherapy. Patients participate in structured group sessions and practice activities of daily living, including routines for house cleaning, eating, and sleeping. They receive individual sessions with psychologists, doctors, and social workers and participate in team meetings and social training. Physical exercise, including strength training, ball games, walks, and running, are part of the usual treatment program. Before admission to treatment, all patients complete detoxification.

Recruitment took place at the treatment centers, where patients were given information and invited to participate in the study by members of the research group and a local project coordinator. All participants were diagnosed with a SUD based on the International Classification of Diseases, Tenth Revision (ICD-10), were inpatients at one of the treatment centers, and were 18 years or older.

### Study Design and Randomization

This study is a short-term, multicenter randomized controlled trial with a single pretest and multiple posttests. Using a crossover design, changes in mood, craving, state anxiety, affect, and self-esteem were assessed by comparing the initial measurement (taken immediately before exercise) with 4 follow-up assessments, first immediately after exercise, then at 1, 2, and 4 hours postintervention. The design allows the pattern of change over time to be seen.

Participants completed 3 sessions—2 supervised group exercise sessions (soccer and circuit training) and 1 control condition (attending a lecture about the health benefits of physical activity)—within the same week. All the sessions were performed in a group setting.

The order of the study conditions was determined by a random number generator and placed in sealed envelopes at a site separate from the study location. When a group of suitable patients (5-10 patients) was recruited at a site, a sealed envelope with the order of exercise and control conditions was drawn by a person outside of the research group.

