#### Baseline and Follow-up Assessments

Mood (primary outcome), craving, affect, self-esteem, and state anxiety were measured with self-report questionnaires. The same questionnaires were repeated for baseline and follow-up assessments. The questionnaires chosen could be completed in 5 minutes, were amenable to repeated administration, and had sound psychometric properties.

The self-report questionnaires and saliva samples collected immediately before the sessions were the baseline assessment. Following the sessions, participants filled in self-report questionnaires on 4 occasions: immediately after the session and 1, 2, and 4 hours after the session. Immediately after the exercise sessions, participants were also asked to rate the perceived intensity. A saliva sample was gathered 4 hours after all sessions. Figure 2 illustrates the SPIRIT figure, study measures, and assessment time points.

Self-report measures were (1) the Feeling Scale, (2) drug craving, (3) the Positive and Negative Affect Schedule (PANAS), (4) the Rosenberg Self-Esteem Scale, (5) state anxiety, and (6) the Borg Rating of Perceived Exertion (RPE) scale.

First, changes in mood related to exercise were assessed with the Feeling Scale [39] (primary outcome), a single-item Likert scale ranging from –5 (very bad) to 5 (very good). Participants were instructed to indicate how they felt “at this moment.” The scale has been used extensively in acute exercise studies [40].

Second, drug craving was assessed using a single-item visual analog scale (VAS) ranging from 0 (no craving for drugs) to 10 (strong craving for drugs). Participants were instructed to indicate how strong their craving for drugs felt “at this moment.” The instrument has been used in previous studies of acute exercise [41] and it was tested in our recent pilot study [36], where it was shown to be sensitive to change.

Third, the PANAS assesses 2 dimensions of affect [42]. Participants self-rate 20 items on a 5-point Likert scale ranging from 1 (very slightly/not at all) to 5 (extremely). Ten of the items represent positive affect and the others represent negative affect.

Fourth, self-esteem was measured using the 10-item Rosenberg Self-Esteem Scale [43], which measures global feelings about oneself (that is, both positive and negative feelings). All items are answered using a 4-point Likert scale ranging from strongly agree to strongly disagree.

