### Statistical Analyses and Power Calculation

Statistical power was estimated using G*Power (version 3.1.9.7; Heinrich-Heine-Universität Düsseldorf). Parameters were based on results from our feasibility study [36] and also took into account previous studies demonstrating medium effect sizes for acute exercise on mood states [38,45]. Assuming an effect size of 0.3 and power (β) of .8, with 3 groups and 5 measurement points, we estimate needing at least 21 participants to test our hypotheses. We planned to include one group of 5 to 10 participants from each site, which would give us 20 to 40 participants. Due to the experimental study design and the inclusion of only inpatients, we anticipate minimal missing data. Descriptive data will be calculated for each measure. Changes over time will be assessed using mixed (group × time) repeated-measures analysis of variance with post hoc contrasts. If participants return questionnaires with missing data, the missing items will be imputed using the last observation carried forward method. If questionnaires are returned with more than 50% of data missing, the questionnaire will be excluded from the analysis.

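### Using the pre-session score as a time level rather than as a covariate is valid, but it loses precision that the scores already collected could give

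*Protocol article*

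**What the plan says.** The section Study Design and Randomization says that effects are assessed by "comparing the initial measurement (taken immediately before exercise) with 4 follow-up assessments". The section Statistical Analyses and Power Calculation fixes the model: "Changes over time will be assessed using mixed (group × time) repeated-measures analysis of variance with post hoc contrasts". The sample size rests on the same structure: "with 3 groups and 5 measurement points, we estimate needing at least 21 participants to test our hypotheses".

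The section Baseline and Follow-up Assessments shows where the five points come from. "The self-report questionnaires and saliva samples collected immediately before the sessions were the baseline assessment", and the follow-up questionnaires are completed "immediately after the session and 1, 2, and 4 hours after the session". One pre-session and four post-session scores make five, so the baseline is itself a level of the time factor. The article nowhere names it as a covariate.

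**The concern.** In a group × time model with baseline as the first time level, the interaction contrast between a follow-up and baseline equals the change under exercise minus the change under the lecture. A change score subtracts the whole pre-session score, including its measurement error. Covariate adjustment subtracts only the part of the pre-session score that predicts the post-session score. Unless the two are almost perfectly correlated, the change-score contrast is noisier.

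This matters here for two reasons. The primary outcome (the Feeling Scale) and the craving and anxiety scales are single items, for which a very high pre-post correlation cannot be taken for granted. The trial also has 39 patients and asks whether two forms of exercise differ from each other, a contrast that may well be smaller than exercise against lecture. What is at stake is precision in every between-condition contrast.

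**Working it through.** **Inputs from the article.** 3 conditions; 5 measurement points (1 pre, 4 post); effect size 0.3; power 0.8; stated minimum 21; 39 patients took part; one order drawn per group of 5 to 10 patients.

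**Assumed, because the article does not state them.** Two-sided alpha 0.05; correlation among repeated measures 0.5; sphericity epsilon 1; effect size read as Cohen's f.

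**Step 1: reproduce the stated 21.** For the within-between interaction, λ = f²·N·m/(1 − ρ), df1 = (k − 1)(m − 1) and df2 = (N − k)(m − 1), with k = 3 and m = 5.
- N = 19: λ = 0.09 × 19 × 5/0.5 = 17.1, df 8 and 64, power 0.806. This is the smallest N that reaches 0.80.
- Rounded up to three equal groups, N = 21: λ = 18.9, df 8 and 72, power 0.856.

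The stated 21 is reproduced under these assumptions as a 3 × 5 interaction. This supports reading the pre-session score as a level of time.

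**Step 2: variance ratio for one follow-up.** Take pre- and post-session scores with variance 1 within patients and same-day correlation r.
- Change score: variance per session 2(1 − r).
- Adjusted score: variance per session 1 − r².
- Ratio: (1 − r²)/[2(1 − r)] = (1 + r)/2, which is below 1 whenever r < 1.

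| r (assumed) | adjusted/change variance | change-score patients that 39 are worth |
|---|---|---|
| 0.3 | 0.65 | 39/0.65 = 60 |
| 0.5 | 0.75 | 39/0.75 = 52 |
| 0.7 | 0.85 | 39/0.85 = 46 |
| 0.9 | 0.95 | 39/0.95 = 41 |

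The slope has to be estimated, which costs a little. In a simulated three-session crossover with 39 patients and patient effects, the ratio was 0.51 to 0.95 for within-patient r from 0 to 0.88, so it stayed below 1 throughout.

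**Step 3: power for one exercise-lecture contrast.** Effect 0.5 SD, N = 39, r = 0.5, unit SD, sessions independent, two-sided t test at 0.05.
- Change: contrast variance 2 × 2(1 − 0.5) = 2.0; SE = √(2.0/39) = 0.226; 0.5/0.226 = 2.21; power about 58%.
- Adjusted: contrast variance 2 × (1 − 0.25) = 1.5; SE = √(1.5/39) = 0.196; 0.5/0.196 = 2.55; power about 70%.

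**Step 4: shared group-session variation.** Sessions are run in groups, and individual pre-scores do not remove variation that a whole group shares after a session. As an illustration, take 5 groups of 8 (40 patients), r = 0.5, and an assumed shared post-session variance g. The ratio is (1.5/40 + 2g/5)/(2.0/40 + 2g/5).
- g = 0: 0.0375/0.050 = 0.75
- g = 0.1: 0.0775/0.090 = 0.86
- g = 0.3: 0.1575/0.170 = 0.93

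The gain shrinks as g grows but keeps its direction.

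**The case against.** The planned ANOVA is a standard and valid analysis. It serves the stated aim of showing the pattern of change over time, and the trial was sized for it: 39 patients took part against a stated minimum of 21. It also gives within-condition change directly, which the hypothesis of improvement after exercise uses. All of that stands, and it makes this a point about efficiency. It does not remove the gain: the time pattern stays estimable from the four post-session scores, and exceeding a minimum is no reason to discard information.

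It could also be said that a condensed article leaves covariates to a fuller plan. Here, however, the article states both the comparison and the model, and counts the baseline among the time points.

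Two further objections limit the size. No correlation is given, and at r = 0.9 only about 5% of the variance is saved. Drawing one order per group can shrink the gain further (step 4).

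A reader might infer that the planned contrast is also distorted, because patients anticipate the coming session, because orders are unbalanced over weekdays, or because scores sit at the ends of their scales. The documents do not support this. They do not say when patients learned the order, which orders were realised, or how scores were distributed. Nor would a linear covariate cure floor or ceiling effects, and if anticipation did shift the pre-scores, neither analysis would be automatically unbiased.

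**Conclusion.** The point holds as a loss of precision. It shows neither bias nor an excess of false positives. The direction is secure for any r below 1 when pre- and post-session variances are equal. The size rests on an unknown r: a variance saving of 35%, 25%, 15% or 5% for one follow-up at r = 0.3, 0.5, 0.7 or 0.9, before any reduction for shared group-session variation. The figures of 58% and 70% apply to one exercise against the lecture, for an assumed 0.5 SD effect, r = 0.5, unit SD and independent sessions. They are not the trial's power under its own assumptions. The improvement is worth making because it needs no new data.

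**What to change.** For the self-report outcomes, replace the five-level ANOVA with a mixed model for the four post-session scores (0, 1, 2 and 4 hours). Include condition, time, condition × time, period and a random patient effect. Enter the session's pre-score as covariate in two parts: the patient's mean over the three days, and that day's deviation from it. The split and the period term are needed because pre-scores in the second and third sessions follow an earlier condition. Report within-condition change from baseline descriptively.

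Cortisol has only one post-session sample, so use the 4-hour value as a single outcome with that day's pre-session value as covariate.

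The cost is a change of analysis wording and a dated record of it. Data collection ended in August 2019 and analysis was planned for 2020, so the record should state that the change was made after collection and before analysis.

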### Procedure

Patients were invited to attend an information meeting, where members of the research group explained the purpose of the study in detail and handed out written information. To minimize dropout, the recruitment took place a maximum of two weeks ahead of the trial. A member of the research group visited the treatment center 1 week before the study to answer questions.

After giving informed consent, eligible participants were gathered to perform the interventions and assessments. These sessions were undertaken on-site at the clinics starting at 9:30 AM on Monday, Wednesday, and Friday within one week. The participants were asked to refrain from doing exercise on the days of the trial and on the days in between the interventions to give a 1-day washout period between the sessions. All sessions lasted 45 minutes. During the week of the trial, all participants received treatment as usual between the sessions.

The following exercise activities and control condition were tested in random order: (1) indoor soccer, (2) circuit training in a gymnasium using body weight, and (3) the control condition, attending a lecture on exercise and mental health.

Across all trial days, the participants were advised to eat breakfast about an hour before starting the trial. They were advised to have a light meal or snack after training, have lunch on all trial days, and keep hydrated throughout the day. Participants were also asked to limit the use of caffeine and nicotine during the test period. The flow of participants through the trial is shown in Figure 1.

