## Results

Data collection was completed in August 2019. In total, 39 patients admitted at 3 treatment centers participated in the study. Data will be analyzed during 2020.

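### Condition order is randomised once per recruited group (about 4 to 7 units), but the named ANOVA works at patient level with no term for recruited group, shared session or day

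*Protocol article*

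**What the plan says.** **Allocation.** Study Design and Randomization describes the step in these words: "group of suitable patients (5-10 patients) was recruited at a site, a sealed envelope with the order of exercise and control conditions". Each recruited group thus gets one envelope, and so one order. The same section adds: "All the sessions were performed in a group setting".

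**Timing.** Procedure: sessions ran "starting at 9:30 AM on Monday, Wednesday, and Friday within one week". Within a recruited group, each condition therefore sits on exactly one weekday.

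**Outcome.** Study Design and Randomization measures change from an assessment just before the session to four assessments after it, on the same day.

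**Numbers.** Statistical Analyses and Power Calculation: "We planned to include one group of 5 to 10 participants from each site", giving 20 to 40 patients, with at least 21 needed. Results: "In total, 39 patients admitted at 3 treatment centers participated in the study". The number of recruited groups and the orders they drew are not given.

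**Analysis.** Statistical Analyses and Power Calculation: "Changes over time will be assessed using mixed (group × time) repeated-measures analysis of variance with post hoc contrasts". In that sentence the word group can only mean the study condition. No term for recruited group, session, day or order is named.

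**The concern.** An analysis should respect the unit that was randomised. Members of a recruited group play the same match, do the same circuit and hear the same lecture on the same day, so whatever makes one session go well or badly moves 5 to 10 patients together. A patient-level ANOVA counts those patients as separate evidence on the difference between conditions.

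The same model has no day term. If mood or craving changes over the morning differently on Mondays than on Fridays, an uneven spread of conditions over weekdays passes part of that difference into the condition contrast.

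This affects the primary outcome (the Feeling Scale) and every comparison of soccer, circuit training and lecture. A p-value that looks like evidence from 39 units may rest on 4 to 7.

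**Working it through.** **1. The plan's own figure.** Inputs stated: effect size 0.3 (taken as Cohen's f), power 0.80, k = 3 groups, m = 5 measurements. Not stated, so assumed: alpha 0.05, correlation among repeated measures 0.5, sphericity. For a within-between interaction:

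- noncentrality = f² × N × m / (1 − 0.5) = 0.09 × 21 × 5 / 0.5 = 18.9
- df = (3 − 1)(5 − 1) = 8 and (21 − 3)(5 − 1) = 72
- power = 0.856. The smallest N reaching 0.80 is 19, which becomes 21 with three equal groups.

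The stated 21 is reproduced. A within-factor test with correlation 0.3 also gives 21, so the exact route is not certain. Both are patient-level calculations with no allowance for allocation by recruited group.

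**2. Number of randomised units.** If groups stayed within 5 to 10, the minimum is 39/10 rounded up = 4 and the maximum is 39/5 rounded down = 7. One group per site cannot have held, since 3 centres × 10 = 30, which is below 39.

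**3. Effect of shared sessions on a within-patient ANOVA.** Set the total variance of a change score to 1, with 0.3 between patients (within-person correlation 0.3, assumed) and a share ICC due to the shared session (assumed, since the article gives none). Patient differences cancel within patient, so the relevant share is λ = ICC / (1 − 0.3). With mean group size n, the variance of a condition contrast is understated by about D = 1 + (n − 1)λ.

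The test has 2 and 2 × 38 = 76 df, with 5% critical value 3.117. For 2 numerator df, P(F > x) = (1 + 2x/76)^(−38), so the actual error is roughly that expression at x = 3.117/D. Example (4 groups, ICC 0.05): n = 39/4 = 9.75, λ = 0.05/0.7 = 0.0714, D = 1 + 8.75 × 0.0714 = 1.63, x = 1.92, error 15%.

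| Groups | ICC | D | Error, formula | Error, simulation |
|---|---|---|---|---|
| 4 (n = 9.75) | 0.02 | 1.25 | 9% | 10% |
| 4 | 0.05 | 1.63 | 15% | 16% |
| 4 | 0.10 | 2.25 | 26% | 28% |
| 7 (n = 5.57) | 0.02 | 1.13 | 7% | 7% |
| 7 | 0.05 | 1.33 | 10% | 10% |
| 7 | 0.10 | 1.65 | 16% | 17% |

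At ICC 0 the simulated error is 5%. If the ICC is instead taken as a share of session plus residual variance only, with patient variance half the residual, the 4-group figures are 8%, 12% and 20%. An ANOVA on group means (2 and 6 df with 4 groups) stays at about 5% throughout.

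**4. The other reading of the named model.** If the three conditions are coded as independent groups, as the power inputs suggest, pairing is ignored and the error term is too large. With 4 groups and within-person correlation 0.3, the simulated error is about 2% at ICC 0, then 3%, 7% and 16% at ICC 0.02, 0.05 and 0.10.

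**5. Day.** With no session correlation, a day effect on the change of −0.25, 0 and +0.25 SD over Monday, Wednesday and Friday gives about 18% error in the within-patient ANOVA with 4 groups and about 12% with 7.

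How uneven the weekdays are depends on how envelopes were drawn, which the article does not say. For 4 groups:

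| | Drawn independently (6⁴ = 1,296 sets) | Four different orders (360 sequences) |
|---|---|---|
| Lecture missing from a weekday | 56% | 20% |
| Every condition on every weekday | 17% | 40% |
| Some condition on one weekday in all groups | 10% | 0% |

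With 7 groups drawn independently, the lecture misses a weekday in 17% of draws (1 − 1,806/2,187).

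**The case against.** The strongest reply is that this is a condensed article. Random effects, covariates and degrees-of-freedom methods usually belong in an analysis plan, and a crossover already removes much of the clustering. Part of that stands: a constant difference between recruited groups cancels, and a fuller plan could add the missing terms. It does not answer the mismatch, because the article names a specific model that does not follow the allocation it describes, and its sample size was reached in the same patient-level way.

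Four stronger readings are tempting, and the documents do not support them:

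- **That the intervals are certainly too narrow.** This needs a positive correlation between session-mates' changes. The article gives no such figure, and under the independent-groups coding the test can be conservative.
- **That condition is confounded with weekday.** This is complete only inside one recruited group. Each group draws its own order, so across groups the confounding is partial and due to chance.
- **That weekday differences in mood or craving enter the contrast.** A constant difference in level is removed by the same-day assessment before the session. Only day differences in the change remain.
- **That the orders were unbalanced by design.** The article mentions a random number generator and sealed envelopes. It neither states nor rules out balancing or drawing without replacement.

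**Conclusion.** The point holds in conditional form. Allocation is by recruited group, with about 4 to 7 units if groups stayed within 5 to 10 patients, while the named ANOVA and the sample size of 21 treat patients as the independent unit. If session-mates' changes correlate, a within-patient ANOVA overstates precision at any positive ICC, and the table above gives the size. If conditions are coded as independent groups, the error runs from conservative to inflated as the ICC rises. That coding would be a second mis-specification in a crossover, not a safeguard. The day problem is secondary: it depends on the orders actually drawn and on whether change differs by weekday.

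The ICC values, the within-person correlation of 0.3 and the day effect are assumptions; the allocation unit and the named model are on the page. The point should be settled before analysis, because it bears on the primary outcome and, by the article's Results section, the data were still to be analysed.

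**What to change.** Replace the ANOVA with a linear mixed model containing condition × time, recruited group, day (period), a random participant effect and a random group-by-session effect, with a small-sample degrees-of-freedom correction. Confirm the primary contrast with a group-level analysis, either on group means or by permutation. A permutation test must follow the envelope scheme actually used; the 1,296 sets apply only to four orders drawn independently. Report the number of recruited groups and the order each one drew.

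The change needs only analysis wording and code, with no new data. It does cost precision. With 4 groups there are 12 sessions, and after the mean (1), groups (3), conditions (2) and days (2), 12 − 8 = 4 session-level degrees of freedom remain; with 7 groups, 21 − 11 = 10. If the lecture fell on the same weekday in every group, its effect cannot be separated from that day. In that case, report the group-level analysis without the day term and state the limitation.
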